##### Train-the-Trainer Education Package

Clinical champions will be encouraged to form their own local implementation team consisting of themselves and at least a medical doctor, and a speech pathologist, from the stroke unit/stroke service with expertise in acute stroke patient management. The clinical champions will receive all components of the online FeSS education package relevant to their study group allocation. Clinical champions will have continued access to the online FeSS education package throughout the duration of the project to support them in implementing the FeSS Protocols.

##### Clinician Education Package

Clinical champions will be responsible for educating all clinicians (nurses, doctors and speech pathologists) in their stroke units/stoke services. They will run the on-site multidisciplinary education session multiple times to reach the majority of clinicians. Clinical champions will use the online education resources to explain to stroke unit/stroke service clinicians about the seven monitoring and treatment elements of the FeSS Protocols (Table 2) and implementation of the Protocols. A detailed explanation of the research evidence underpinning the FeSS Protocols including the rationale for its inclusion in the stroke guidelines will also be provided at the session. Clinical champions will be permitted to share modules from the online education package with the clinicians who are unable to attend the session and arrange make-up training.

#### FeSS audit and feedback report

Clinical champions in intervention hospitals will receive a confidential online baseline report of their pre-implementation audit data on FeSS Protocol compliance prior to the intervention. They will be provided with one post-implementation audit report about 2 weeks following completion of the post-implementation audit. Intervention group hospitals will receive detailed reports which provide information on the implications of the findings as well as recommendations for improvement. This report is designed to meet the fifteen recommendations believed to be associated with effective audit and feedback interventions [58]. We used this report in our previous QASC Europe project [17, 20], and after obtaining end-user feedback, it was refined for use in the current study. We have also successfully pilot tested the report with stroke nurse experts.

#### External remote facilitation

Three researchers with health qualifications and expertise in stroke research will provide external online only (i.e. no site visits) remote facilitation to intervention hospitals. Their role will involve providing information about the study to participating hospitals and granting intervention hospitals access to the online education package. They will guide clinical champions in the high-intensity external remote facilitation intervention group in undertaking self-directed training to develop their capability and capacity in leading and negotiating evidence-based change. Clinical champions in the low-intensity external remote facilitation intervention group will not receive guidance from the external facilitators but will be provided with the flowchart of project milestones to ensure they undertake the audit training within the specified timeframe. The external facilitators will also support intervention hospitals in the high-intensity external remote facilitation group via videoconference sessions (described below; Table 4) but will not be involved in data collection.

**Table 4 Tab4:** Time points for 1-h external facilitation videoconference sessions

• Post-randomisation - To discuss pre-implementation audit results and the online FeSS education package • After clinical champions receive the online FeSS education package - To discuss progress with completing the package • After clinical champions conduct the multidisciplinary meeting - To assist with action plan development • At commencement of 3-month bedding down period - To discuss any issues with FeSS Protocol implementation	

#### Videoconference sessions

The three external facilitators will lead the videoconference sessions, comprised of a didactic component using standardised PowerPoint slides, and inter-active group participation. These sessions will be target clinical champions in the high-intensity external remote facilitation intervention group. Sessions will be delivered in groups and the number of clinical champions in a group will depend on their availability to attend a scheduled session. A minimum of four, 1-h videoconference sessions are planned (Table 4). These will be held at key project milestones, specifically post-randomisation (to discuss pre-implementation audit results and the online FeSS education package); after receiving the online FeSS education package (to discuss progress with completing the package); after the multidisciplinary meeting (to assist with action plan development); and at commencement of the 3-month bedding down period (to discuss any issues with FeSS Protocol implementation). Sessions will be repeated as many times as necessary to ensure all clinical champions receive the same high-intensity dose of external remote facilitation. Any additional sessions and their timing will be determined by demand from the clinical champions group.

#### Local team meeting to assess barriers and develop action plan

Clinical champions in intervention hospitals will be provided with resources from the online FeSS education package to conduct a local multidisciplinary meeting to identify barriers and enablers to the FeSS Protocol uptake. A detailed baseline pre-implementation audit and feedback report of FeSS processes of care will be presented by the clinical champion(s) at the meeting as the evidence base for current standard of care for stroke patients at the hospital. The meeting will be used by stroke unit/stroke service teams to work together to identify potential barriers and enablers to implementation of the FeSS Protocols and develop an Action Plan with local solutions. The clinical champions will be provided with an Action plan template previously piloted in the QASC and T^3^ Trials [1, 59], and developed using the model suggested by French and colleagues [50]. This Action plan will be sent to the researchers at the Nursing Research Institute and will be used to guide the external remote facilitation videoconference sessions held by the researchers for intervention hospitals in the high-intensity external remote facilitation intervention group.

#### Reminders

The high and low facilitation intervention group hospitals will be sent intervention reminders (Table 5) to prompt them to progress with FeSS Protocol implementation.

**Table 5 Tab5:** Timepoints and details of reminders

Milestone	First email	Second email	Third email^**a**^
***Project process reminders (high- and low-intensity intervention group and control group hospitals)***			
EOI received to participate in study	Email to sign Agreement Form, nominate clinical champion(s), complete organisational survey online and assist with obtaining site-specific governance approval	Two weeks later same email if no response	Two weeks later same email if no response
Site-specific governance approval received	Confirmation email sent		
***Data collection reminders (high- and low-intensity intervention group and control group hospitals)***^*******^			
Pre-implementation audit	Email sent 1 week before pre-implementation audit date (3 months post-study commencement) with data entry instructions	Email sent 2 weeks after pre-implementation audit date if no data entry	Email sent 4 weeks after pre-implementation audit date if no data entry
Completion of pre-implementation audit and data queries from statistician	Confirmation email sent with any requests for data checks (if required) based on preliminary data cleaning 1 week after completion of audit		
Reliability cases sent to hospitals for data checks	Email sent requesting data reliability checks 1 week after completion of audit	Email sent 2 weeks later if no response	Email sent 2 weeks later if no response
Pre-implementation audit and feedback report	Email sent with report 2 weeks after completion of audit		
Post-implementation audit	Email sent on post-implementation audit date (6 months post-implementation)	Email sent 4 weeks after post-implementation audit date if no data entry	Email sent 6 weeks after post-implementation audit date if no data entry
Completion of post-implementation audit and data queries from statistician	Confirmation email sent with any requests for data checks (if required) based on preliminary data cleaning 1 week after completion of audit		
Reliability cases sent to hospitals for data checks	Email sent requesting data reliability checks 1 week after completion of audit	Email sent 2 weeks later if no response	Email sent 2 weeks later if no response
Post-implementation audit and feedback report	Email sent with report 2 weeks after completion of audit		
***Intervention reminders (high-intensity and low-intensity intervention group hospitals only)***			
FeSS Protocol implementation	Email sent requesting multidisciplinary meeting date/s	Email sent 2 weeks later if no response	Email sent 2 weeks later if no response
Action plan	Email sent requesting action plan	Email sent 2 weeks later if no response	Email sent 2 weeks later if no response
FeSS Protocol implementation ‘go-live’ date	Email sent 1 month after meeting requesting ‘go-live’ date	Email sent 1 month later if no response	Email sent 2 weeks later if no response

^a^Further email prompts may be required; ^*^Control group hospitals do not receive emails with the audit and feedback report

#### Email and telephone support

The researchers will provide clinical champions from the intervention group hospitals with ongoing proactive and reactive email and telephone remote support (Table 6).

**Table 6 Tab6:** Email and telephone external remote support^a^

***Email*** ▪ Proactive emails from research team to clinical champions during key milestones (post-randomisation; post-receipt of online FeSS education package; post-multidisciplinary meeting; commencement of 3-month bedding down period) ▪ Reactive emails from clinical champions to research team when required ***Telephone*** ▪ Proactive telephone contact from research team to clinical champions following completion of pre-implementation audit data collection ▪ Reactive telephone contact from clinical champions to research team when required	

^a^High-intensity external remote facilitation (proactive and reactive); low-intensity external remote facilitation (reactive only)

### Control group

Hospitals randomised to the control group will only have access to the publicly available FeSS Protocols. No active intervention/external remote facilitation will be provided by the researchers, and these hospitals will perform usual stroke care practices and collect data on the FeSS processes of care. Control group hospitals will not receive the detailed FeSS audit and feedback reports that will be provided to intervention group hospitals. However, there may be some hospitals randomised to the control group that participate in the biennial national stroke acute care audits and/or contribute continuous data on the FeSS elements to the AuSCR. As per standard practice, these hospitals will routinely receive basic audit and feedback reports from the Stroke Foundation and/or AuSCR as part of quality improvement initiatives undertaken external to the trial. If the research team receive any proactive emails from control group hospitals regarding the study (excluding questions about data collection), these hospitals will be directed to the Quality in Acute Stroke Care webpage hosted on the Australian Catholic University website (https://www.acu.edu.au/qasc). If the questions relate to the national stroke audit or AuSCR data entry or platform issues, they will be referred to the national stroke audit coordinator or AuSCR, as required. At study completion, clinical champions from control group hospitals will receive access to the online FeSS education package after providing their post-implementation data.

### Data collection

Pre- and post-implementation data will be entered by hospital staff into the web-based Australian Stroke Data Tool or directly into the New Zealand Stroke Registry, for Australian and New Zealand hospitals respectively. The Australian Stroke Data Tool is an integrated data management system used to collect patient data for the Stroke Foundation national audits and the Australian Stroke Clinical Registry [60]. Access to the data is password protected and the server has an effective firewall and security policies that are regularly reviewed and maintained to ensure adherence to all local and national privacy laws and principles. Medical notes of up to 100 eligible patients or 6 months of eligible stroke patient data will be retrospectively reviewed for the pre-implementation audit. For the post-implementation audit, hospital staff will be required to undertake medical record audits for 100 prospective consecutive stroke admissions or up to a period of 6 months, providing data for similar numbers of patients pre- and post-implementation. Demographic and clinical data to be obtained include the following: hospital name, patient medical record number, age, sex, date of stroke onset, date of admission, stroke type, stroke severity using the National Institutes of Health Stroke Scale [61], premorbid risk factors and functional status using the modified Rankin Scale score [62], treatment in a stroke unit, FeSS variables, discharge modified Rankin Scale and discharge destination.

Clinicians from participating hospitals will receive video instructions on how to undertake a medical record audit and enter data into the Australian Stroke Data Tool for uniformity in data collection processes. All participating hospitals will be sent project process and data collection email reminders by the research team at critical timepoints during the project (Table 5). Hospitals in the control group will undertake data collection at the same time as the intervention hospitals with which they are blocked randomised.

Participating hospitals will also be asked to complete a short online organisational survey to obtain information about structural workplace characteristics and resources available to deliver acute stroke care to allow for more accurate data comparison. Data to be collected include presence of stroke unit, bed capacity, availability of multidisciplinary and specialist staff, annual thrombolysis rate (previous 12 months) and presence of stroke care facilitators from the Angels Initiative (a not-for-profit organisation that aims to optimise the quality of treatment in stroke centres [https://www.angels-initiative.com/]).

All data will be stored, managed and archived in accordance with National Health and Medical Research Council requirements. Electronic data will be stored on password-protected networked drives linked to the Nursing Research Institute and accessible only by the researchers. The final trial data set will be archived in a data repository. Only de-identified data will be analysed. The study findings will be communicated via publication in peer-reviewed scientific journals.

### Study procedure

Following the recruitment process, stroke unit/stroke service coordinators of eligible hospitals who express interest in participating will be sent an email requesting them to sign an Agreement Form indicating hospital consent to participate. They will also be requested to nominate a hospital clinical champion who will complete the online organisational survey and assist with obtaining site-specific governance approval and act as the hospital liaison officer with the researchers. After receipt of this approval, hospitals will be required to complete the pre-implementation retrospective medical record audit following which they will be randomised to one of the two intervention or control groups. From the date of randomisation, the clinical champion(s) of intervention hospitals will be required to undertake the online FeSS education package training and organise a local multidisciplinary barriers and enablers identification meeting. We will request that this training and meeting be completed within 6 weeks of hospital randomisation; however, should this not occur, we will negotiate intervention start dates with these hospitals. Hospitals will then commence a 3-month implementation period which will involve clinical champions running the multidisciplinary barriers and enablers identification meeting, clinician education session and commence implementation of the FeSS Protocols. It is anticipated that the ‘go-live’ date (when the FeSS Protocols are considered normal business and are fully operational) will be scheduled for the end of the 3-month implementation period. Hospitals then will have a further 3 months ‘bedding down’ of the intervention for it to become routine practice [1] following which the post-implementation prospective medical records audit will be commenced. Further details about the trial enrolment, interventions and assessments are shown in Table 7.

**Table 7 Tab7:** Schedule of enrolment, interventions and assessments

TIMEPOINT	Study period							
	Pre-intervention activities	Randomisation	Intervention			Post-intervention activities		Close-out/completion of trial
	Q4 2022	Q1 2023	Q2–Q4 2023			Q4 2023–Q3 2024		Q4 2024
**ENROLMENT:**	x	x						
Eligibility screen	x	x						
Informed Agreement	x	x						
HREC and Governance applications	x	x						
Baseline data collection	x	x						
Randomisation of hospitals		x						
**INTERVENTION**			**High facilitation**	**Low facilitation**	**Control**			
Baseline audit and feedback report			x	x				
Email FeSS Protocols					x			
Videoconference 1			x					
Email link to online FeSS education package			x	x				
Videoconference 2			x					
Multidisciplinary Team barrier assessment workshop (Action plan development)			x	x				
Videoconference 3			x					
Education sessions for stroke unit/stroke service clinicians			x	x				
Recruitment of clinicians for process evaluation interviews and focus groups			x	x	x			
Videoconference 4			x					
**3 months bedding down of FeSS Protocols**			x	x	x			
Post-intervention audit data collection			x	x	x	x		
Post-intervention audit and feedback report			x	x				
**ASSESSMENTS**								
Overall FeSS adherence composite measure	x					x		
Individual monitoring and treatment elements of the FeSS Protocols	x					x		
Death and dependency (mRS) *sub-study only*	x					x		
EQ-5D-3L questionnaire *sub-study only*	x					x		
Costs of implementing the FeSS Protocols	x	x	x	x	x	x	x	x
**Process evaluation interviews and focus groups**						x	x	
**Economic evaluation**						x	x	x

### Economic evaluation

An economic evaluation will include a cost-consequence analysis to evaluate the costs and benefits of the external remote facilitation (low and high) interventions, relative to control. We will also assess the potential cost-effectiveness of the interventions compared with control by estimating incremental cost-effectiveness ratios (ICERs) [63]. All costs will be presented based on the 1-year period of the QASC Australasia programme. Cost will be converted into Australian/New Zealand dollars using a nominal rate method and adjusted for inflation where necessary. The additional costs of implementing the FeSS Protocols will be informed by financial records kept by the researchers. Other additional costs or cost savings due to the implementation of the FeSS Protocols will be considered based on the findings of the clinical evaluation, the findings of the process evaluation, and consultation with the researchers.

Data on health benefits will be derived in a sub-study of this cluster randomised controlled trial. This sub-study will only include trial hospitals that contribute data to the AuSCR [64] or the New Zealand Stroke Registry because the registries collect 90–180-day patient outcome data required for the economic evaluation. For this subset of hospitals contributing FeSS data to the registry [64], patient hospital data collected in the Australian Stroke Data Tool together with the follow-up survey data collected between 90 and 180 days from the AuSCR will be used. Quality-adjusted life years (QALYs) will be estimated by applying utility scores according to the modified Rankin Scale at discharge from hospital, from data obtained at a follow-up assessment conducted at 90–180 days post-stroke as part of the AuSCR and survival status determined through routine linkage of the AuSCR with the National Death Index. Responses to the EQ-5D-3L questionnaire at 90–180 days post-stroke will be converted into a utility score using an algorithm developed in an Australian population [65].

Data from the study will be supplemented in the economic analysis models by applying estimates from the published literature on treatment effect, discharge destination and outcomes, as required. The economic evaluation will be reported according to the Consolidated Health Economic Evaluation Reporting Standards [66], and the findings may be used to model the potential benefits of FeSS implementation state-wide or Australia-wide.

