There are many ways of providing facilitation which vary in their intensity, and level of resources required [10–15]. However, there is relatively little information about the effectiveness and cost-effectiveness of different facilitation models [13, 22, 23]. In particular, it is important to evaluate low-intensity/resource and high-intensity/resource approaches to identify effective and affordable facilitation models. Building on our previous research, this study will develop and test two different intensities of external remote (no face-to-face hospital visits by the research team) facilitation to support delivery of the FeSS Protocols for patients with stroke, at pace and on a large scale in two countries. Implementation of the FeSS Protocols will be informed by an integrated knowledge translation model [24]. This model incorporates evidence-based behaviour change implementation strategies (an online education package, audit and feedback reports, local clinical champions, barrier and enabler assessments, action plans, reminders and external remote facilitation) [25] and frameworks (Theoretical Domains Framework [TDF] [26], Capability, Opportunity, Motivation – Behaviour Model (COM-B system) [27] and the Consolidated Framework for Implementation Research [28]).

Cost-effectiveness studies evaluating the use of implementation strategies, including facilitation, in acute care settings are limited [29]. A study investigating changes in acute hospital costs before and after implementation of a stroke clinical facilitator programme found that the average cost per bed-day was higher post-implementation (AUD $878 per day) compared to pre-implementation (AUD $709). However, there was subsequent evidence of cost containment, with the average total inpatient costs per-episode decreasing by 10% over 4 years [30]. An independent economic evaluation estimated a gross economic benefit of AUD $281 million per year if the FeSS Protocols were implemented in 65% of the Australian stroke patient population [31]. A further study showed large societal and healthcare savings costs of AUD $251.7 million and AUD $65.2 million respectively for use of the FeSS Protocols over a 5-year period [32]. Consequently, we also will undertake a sub-study that includes an economic evaluation of the different facilitation strategies for implementing the FeSS Protocols.

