### Study aims

The primary aim is to compare the effectiveness of high-intensity versus low-intensity external remote facilitation to support implementation of the FeSS Protocols to improve management of fever, hyperglycaemia and swallowing difficulties in the first 72 h of stroke unit/stroke service admission in Australia and New Zealand.

The secondary aims are to compare the effectiveness of (1) low-intensity facilitation with no facilitation, (2) high-intensity facilitation with no facilitation and (3) high- or low-intensity facilitation with no facilitation, to support implementation of the FeSS Protocols; (4) determine whether post-intervention changes in monitoring and treatment for fever, hyperglycaemia and swallowing differ between metropolitan and rural/remote hospitals; (5) determine whether post-intervention changes in monitoring and treatment for fever, hyperglycaemia and swallowing differ between stroke units and stroke services; (6) describe the potential cost-effectiveness of the different facilitation methods (economic evaluation); and (7) identify clinicians’ views regarding factors that influence uptake of the FeSS Protocols in metropolitan and rural/remote hospitals (process evaluation).

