The secondary outcome measures are composite outcomes of adherence to each of the combined monitoring and treatment elements for (i) fever, (ii) hyperglycaemia (sugar) and (iii) swallowing protocols, and to the individual elements that make up each of these protocols (Table 8); comparison between metropolitan and rural/remote hospitals for composite outcome of adherence to each of the combined monitoring and treatment elements for (i) fever, (ii) hyperglycaemia (sugar) and (iii) swallowing protocols, and to the individual elements that make up each of these protocols; and comparison between stroke units and stroke services for composite outcome of adherence to each of the combined monitoring and treatment elements for (i) fever, (ii) hyperglycaemia (sugar) and (iii) swallowing protocols, and to the individual elements that make up each of these protocols.

The outcome for the economic evaluation will be the additional cost per quality-adjusted life year gained at 6 months post-stroke due to implementation of the FeSS Protocols. The process evaluation measure is the qualitative exploration of participants’ experience of contributing organisational, contextual and structural factors that impacted successful/unsuccessful uptake of the intervention.

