#### Economic evaluation

Multiple imputation will be used to handle missing data used to estimate costs and quality-adjusted life years. Multivariable regression models will be used to adjust for differences in characteristics between control and intervention cohorts. Differences in costs and quality-adjusted life years gained between groups will be adjusted for confounding factors. Bootstrapping will be undertaken to test the robustness of results. Sensitivity analyses will also be performed to assess the effects of various assumptions in the economic modelling.

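### The economic evaluation sets both facilitation intensities against control and names no high v low contrast, so it does not directly show what high intensity buys over low

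*Protocol article*

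**What the plan says.** The Economic evaluation section of the Methods describes two analyses. The first is "a cost-consequence analysis to evaluate the costs and benefits of the external remote facilitation (low and high) interventions, relative to control". The second is the set of ratios: "We will also assess the potential cost-effectiveness of the interventions compared with control by estimating incremental cost-effectiveness ratios (ICERs". In both, control is the comparator for each intensity.

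The economic part of the Data analysis section keeps that framing: "Multivariable regression models will be used to adjust for differences in characteristics between control and intervention cohorts". Its next sentence is less specific: "Differences in costs and quality-adjusted life years gained between groups will be adjusted for confounding factors". The Outcome measures section defines the economic outcome as "the additional cost per quality-adjusted life year gained at 6 months post-stroke due to implementation of the FeSS Protocols", without naming a comparator.

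The aims are wider. Secondary aim 6 is to "describe the potential cost-effectiveness of the different facilitation methods (economic evaluation", and the Background argues that "it is important to evaluate low-intensity/resource and high-intensity/resource approaches to identify effective and affordable facilitation models". For the adherence outcomes, the Data analysis section does name the high v low comparison alongside the two comparisons with control.

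**The concern.** A hospital or health service will adopt one of three options: no facilitation, low intensity or high intensity. Table 1 shows that high intensity adds videoconferences and proactive contact to what low intensity receives, so it presumably costs more to deliver. The useful question about that extra resource is what it yields beyond low intensity.

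A ratio of high intensity against control does not answer this. It averages the step from control to low with the step from low to high. If the first step is efficient and the second is not, the average can still fall below a funder's threshold. High intensity can even pass against control when low gives the same benefit for less money. A reader shown only two ratios against control could then take both intensities to be good value and miss that the second step is not.

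**Working it through.** The article gives no costs, QALY gains or willingness-to-pay threshold, and no economic figure to reproduce. All values below are assumptions, per patient and relative to control, chosen to test the logic.

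**Formula.** ICER = difference in cost / difference in QALYs.

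**Illustration 1.** Low +$100 and +0.010 QALY; high +$500 and +0.012 QALY.
- Low v control: 100 / 0.010 = $10,000 per QALY.
- High v control: 500 / 0.012 = $41,667 per QALY.
- High v low: (500 − 100) / (0.012 − 0.010) = 400 / 0.002 = $200,000 per QALY.

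At an assumed threshold of $50,000 both intensities pass against control, but the step from low to high fails by a factor of four.

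**Illustration 2, varying the benefit of high intensity.** Low +$200 and +0.010 QALY, so low v control is $20,000 per QALY; high +$450; threshold $50,000.

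| QALY gain, high v control | High v control | High v low | Passes v control | Passes v low |
|---|---|---|---|---|
| 0.010 | 45,000 | no gain, costs 250 more | yes | no |
| 0.012 | 37,500 | 125,000 | yes | no |
| 0.014 | 32,143 | 62,500 | yes | no |
| 0.015 | 30,000 | 50,000 | yes | at the threshold |
| 0.018 | 25,000 | 31,250 | yes | yes |

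**Range of the reversal.** Let q be the QALY gain of high intensity over control and T the threshold. High passes against control when q > 450/T. It fails, or only equals the threshold, against low when q ≤ 0.010 + 250/T. Both hold together over these ranges:
- T = 20,000: 0.0225 to 0.0225, so the range shrinks to a point
- T = 30,000: 0.015 to 0.0183
- T = 50,000: 0.009 to 0.015
- T = 75,000: 0.006 to 0.0133
- T = 100,000: 0.0045 to 0.0125

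The width of the range is 0.010 − 200/T, which is positive whenever low intensity is itself good value against control (here T above 20,000). So the reversal needs no unusual inputs, but a large enough gain from high intensity removes it.

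**What subtraction can and cannot give.** If the cost and QALY differences of each intensity against control are reported, the high v low differences follow: 500 − 100 = 400 and 0.012 − 0.010 = 0.002. Their uncertainty does not follow from the two ratios. The two control contrasts share the control arm and are correlated, and neither ratio carries that correlation or the separate variances of cost and QALYs.

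**The case against.** The best defence is that the text does not exclude a high v low comparison. The Economic evaluation section lists what will be included. The Abstract speaks more loosely of cost differences for each intervention, aim 6 covers the facilitation methods in general, and the Data analysis section refers to differences between groups. A journal article also condenses, and dominance rules or acceptability curves are the kind of detail left to a fuller plan. The data would support the contrast whenever someone asked for it.

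Part of this stands. The wording is not exclusive, and the absence of technical detail is no fault. But where the article does state a comparator, it states control, twice, and none of the looser sentences names high v low. The point concerns that stated choice.

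Four stronger readings are tempting, and the document does not support them:
- **High v low cost-effectiveness is the primary aim.** It is not: "The primary aim is to compare the effectiveness of high-intensity versus low-intensity external remote facilitation" concerns effectiveness, while the economic aim is secondary and descriptive.
- **The control-based ratios will select the wrong intensity.** The Discussion ties its business case to whichever intervention proves most effective, so the ratio is not the stated selection rule.
- **The high v low increment is lost.** Its point estimate can be recovered by subtraction.
- **The small control arm is what makes the plan unsound.** A full incremental analysis normally keeps low v control, so that argument would not be cured by the change and is not relied on here.

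**Conclusion.** The point holds in a limited form. The article fixes control as the comparator for both economic analyses and names no high v low economic contrast, which serves its own secondary aim 6 and its Background rationale poorly. With three mutually exclusive options, high intensity can appear acceptable against control while its increment over low is poor value or dominated.

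No size can be given for this trial, because the result depends on costs, QALY gains and a threshold that are not in the document. In the second illustration, at $50,000 per QALY, the reversal covers gains for high intensity above 0.009 and up to 0.015 QALY; at 0.018 it disappears. The gap affects a secondary, descriptive evaluation and can be closed in the analysis. It should be corrected, but it does not threaten the trial's primary comparison.

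**What to change.** Replace the control-only comparison in the Economic evaluation section with a full incremental analysis:
- order the three arms by cost;
- remove options that are dominated, including by extended dominance;
- compare each remaining arm with the next less costly one, normally low v control and then high v low.

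Report the high v low difference in cost and in QALYs, or the net benefit, with its uncertainty; the bootstrap already planned could supply this if all three arms are resampled together. Add a high v low column to the cost-consequence table, and name the contrast in the economic part of the Data analysis section.

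The same cost and outcome data are used. The cost is a little more analysis. The high v low estimate may be imprecise, and the report should show that openly.
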